#### Infant and Young Child Feeding (IYCF) practices

Data on IYCF practices (breastfeeding and complementary feeding) are collected through a structured IYCF questionnaire, employing 24-h [11] and 7 day recall methods. WHO-recommended core indicators of optimal breastfeeding include early initiation of breastfeeding (within 1 h of birth), EBF till 6 months after birth and continued breastfeeding till at least 2 years post-birth [33]. Information on all these indicators and associated information are collected. Data on early initiation of breastfeeding and pre-lacteal use is collected within 24-h of birth and on the 7th day. EBF information is collected periodically on the 7th day of birth, and then monthly postpartum from 1 to 6 months. Continued breastfeeding information is collected every three months thereafter till 24 months.

WHO-recommended complementary feeding practices include introduction of solid, semi-solid or soft foods; minimum dietary diversity, meal frequency and acceptable diet; and consumption of iron-rich or iron-fortified foods from postnatal 6 completed months [33]. This information is collected every third month from postnatal 6 to 24 months. Comparison of continued breastfeeding and complementary feeding practices will be made between intervention arms and the comparison arm at these time points.

#### Other measurements

Background characteristics of study participants: Information on demographic and socio-economic status (SES), family members, reproductive and morbidity history of pregnant women were collected using a structured questionnaire [25]. Household food security (HFS) information was collected through a questionnaire adapted from food security and nutrition surveillance tool [34]. These were recorded once during recruitment of the pregnant women after consent has been taken, to compare background characteristics between the arms.

Water sanitation and hygiene (WASH) and Knowledge attitude and practice (KAP): A questionnaire on the core indicators on water, sanitation and hygiene (WASH) was developed based on a standard manual for WASH [35]. Woman’s knowledge, attitude and practices (KAP) regarding maternal and child nutrition was developed based on WHO-recommended IYCF indicators and KAP manual [36]. WASH and KAP are collected during pregnancy and postpartum follow up visits.

Childhood morbidity: Morbidity, especially diarrhoea, directly impedes growth, while better hygiene practices lower infectious disease burden [37]. Therefore, children’s morbidity data is collected every month from postnatal 1 to 6 months and every three months thereafter till 24 months, using a 2-week recall questionnaire [11]. Vaccination data would be collected at 12 and 15 months based on EPI schedule.

Additional anthropometric measurements: Mother’s height is measured during recruitment for body mass index (BMI) calculation during early pregnancy. Mother’s mid-upper arm circumference (MUAC) (precision 1 mm), infant’s head circumference (during 1–6 moths age) and infant’s MUAC (during 7–24 months) are collected during follow-up visits, for associated z-score calculations.

### Data collection

All questionnaire-based data and anthropometric measurements are collected by trained data collectors. Anthropometric measurements are taken following measurement-specific standard operating procedure [38]. Measuring tools are calibrated regularly. All data collectors are female and locally recruited. Before initiation of participant recruitment, the data collection team was intensely trained by the central team on all aspects of data collection, including consent taking, different data collection methods, anthropometric measurements, question throwing techniques, use of the tablet and cultural aspects to consider during data collection. Monthly meetings are held for troubleshooting and refresher trainings are conducted as needed. Following the initial training, all data collectors were standardised for anthropometric measurements against two gold standard trainers from icddr,b. Subsequently, refreshers trainings are conducted every two months to retain measurement standards. The data collectors are directly supervised by two FRAs who monitor data collection quality and provide on-site feedback as needed. One field manager is responsible for overall field coordination.

### Project management system for implementation and monitoring

A bespoke automated Project Management Information System (MIS) has been developed linking data collection and intervention delivery through android-based tablet (handheld)-PC with a central database where progress can be monitored by the field supervisors and central staff. On pregnancy enrolment through the tab, an android platform-based application automatically generates subsequent prenatal visit plans and tools at pre-specified schedules and tasks of CHWs and data collectors (intervention modules for CHWs and questionnaire for data collectors). Similarly, birth is registered in the tab immediately upon notification. To ensure post-partum data collection within 24 h of delivery, a mobile phone-based birth-notification system has been established. Enrolled pregnant women and their family members are continuously encouraged to notify birth by text message or voice calls as early as possible, preferably within six hours of birth. Registration of live births then generates appropriate plans and tools for postpartum visits by CHWs and data collectors. The web-linked desktop dashboard system is used to monitor activities/performance of CHWs and data collectors in real time by field supervisors and the central team.

### Process evaluation

#### Adherence to supplements for both mothers and children

Empty supplement sachets are collected and supplement tracking is carried out in each visit by the CHWs. Besides, we are assessing supplement compliance using a structured questionnaire with some open questions with queries on respondents’ attitude and practice towards the antenatal and complementary food supplements provided to them. We would collect similar data for checking compliance of complementary supplements to children aged 6 months to 24 months (in associated arms).

#### BCC monitoring

The BCC modules set in the tablets are customised for each CHW. Date and time of each visit is automatically recorded as the CHW proceeds with the module. The module for each visit has several sub-topics linked to associated details, and timing of these sub-topics is also automatically recorded. These measures ensure an automated machine-based monitoring system from which BCC delivery coverage can easily be tracked and calculated.

### Statistical analysis plan

Data analysis to detect change of the primary outcome (mean LAZ) will be conducted with length measured at 1, 3, 6, 9, 12, 15, 18, 21 and 24 months of age using t-tests assuming LAZ will satisfy the normality assumption. Longitudinal assessment of significance using lag time of stunting (mean length > −2SD below median of WHO reference population) will be done by the log rank test, followed by fitting a Cox proportional hazards model for each intervention arm to determine the change in risk of stunting compared to the comparison arm. Multiple linear regression will be employed to quantify the effect of intervention in each intervention arm compared to the comparison arm in terms of mean LAZ change and some secondary continuous outcome measures including changes in mother’s weight, birth weight, diarrhoea morbidity. Logistic regression will be used on binary outcome variables which comprise most of our secondary outcomes measures (e.g. – EBF and breastfeeding initiation within 1 h of birth). All these models will be controlled for possible confounders (household food security, educational background and SES) if randomisation of the clusters does not control for differences in these factors at baseline. For regression models, we shall consider random effects of clustering. All analysis will be intention-to-treat. Quantitative data analysis will be done using Stata SE 14.2 (StataCorp LP, College Station, Texas, USA).

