**Methods:**

This community-based cluster randomised trial (c-RCT) compares 4 intervention combinations against one comparison arm. Intervention combinations are: 1) Behaviour change communication (BCC) on maternal nutrition during pregnancy, exclusive breastfeeding, and complementary feeding, along with prenatal nutritional supplement (PNS) and complementary food supplement (CFS); 2) BCC with PNS; 3) BCC with CFS; and 4) BCC alone. The comparison arm receives only routine health and nutrition services. From a rural district, 125 clusters were selected and randomly assigned to any one of the five study arms by block randomisation. A bespoke automated tab-based system was developed linking data collection, intervention delivery and project supervision. Total sample size is 1500 pregnant women, with minimum 1050 resultant children expected to be retained, powered to detect a difference of at least 0.4 in the mean LAZ score of children at 24 months, the main outcome variable, between the comparison arm and each intervention arm. Length and other anthropometric measurements, nutritional intake and other relevant data on mother and children are being collected during enrolment, twice during pregnancy, postpartum monthly till 6 months, and every third month thereafter till 24 months.

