**Discussion:**

This c-RCT explores the effectiveness of bundles of *preventive* nutrition intervention approaches addressing the critical window of opportunity to mitigate childhood stunting. The results will provide robust evidence as to which bundle(s) can have significant effect on linear growth of children. Our study also will have policy-level implications for prioritising intervention(s) tackling stunting.

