### Study aim and hypothesis

This study aims to test the effectiveness of the intervention bundle(s) on improving length-for-age Z score (LAZ) of children at two years of age. We hypothesised that our intervention bundle(s) would cause a change of at least 0.4 in mean LAZ of children, translating to at least 30% reduction in stunting in that arm(s), compared to that in the comparison arm.

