Several assumptions were considered for the sample size calculation [26]. The first assumption was that mean LAZ (our primary outcome variable) for 18–23 months old children in the comparison arm will be −2.0, and standard deviation of mean LAZ in both intervention and comparison arms will be 1, based on the mean HAZ reported in this age group in the BDHS 2011. These BDHS 2011 [25] parameters were the latest available during this protocol development. The estimates were still valid in 2015 since the latest BDHS (2014) showed similar stunting rates in *Sylhet* division [11]. Second, a 0.4 difference in mean LAZ score was expected in intervention arms compared to comparison. As the third assumption, we considered an 80% power and 5% alpha; the inter-cluster correlation coefficient of 0.06, derived from the design effect for HAZ in BDHS 2011, was used for adjustment of clustering effects. Fourth, the ratio between 4 intervention and 1 comparison arms was set at 1:1:1:1:1. Taking all the above assumptions into account, the Stata SE 13 software calculated the sample size to be 175 children per arm, which can be yielded from 25 clusters. However, to examine the secondary outcome variables between the comparison arm and individual intervention arm with a higher statistical power, the sample size in the comparison arm was doubled, thus the ratio between participant numbers in each intervention arm and comparison arm was raised to 1:2, respectively. The final allocation ratio of study participants was thus 1:1:1:1:2 for intervention arm 1: intervention arm 2: intervention arm 3: intervention arm 4: comparison arm 5. Thus, the final sample size was 175 children in each intervention arm and 350 children in the comparison arm. Considering the characteristics of the intervention, however, enrolment was during pregnancy. We therefore considered the following losses- 11% pregnancy loss due to abortion and still births (personal communication from Health and Demographic Surveillance System run by icddr,b at Mirzapur, Tangail), a 4% mortality in the first two years of life [25], 15% losses due to non-consent to participate by eligible women and loss-to-follow up. Loss-to-follow up includes refusal and migration out of study area. Thus, final sample size considering participant recruitment during pregnancy was 250 pregnant women in each intervention arm and 500 pregnant women in the comparison arm which is expected to yield the required number of children at 24 months from the enrolled cohort.

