### Trial outcomes and measurements

#### Primary outcomes

The primary outcome measure will be the LAZ of children at 24 months of age based on WHO MGRS 2006 child growth reference. This will be calculated from the child’s age in months and length on associated ages. Length is measured at age 7–10 days, then monthly from 1 to 6 months, and at 9^th^, 12^th^, 15^th^, 18^th^, 21^st^ and 24^th^ months of age, with locally manufactured collapsible length boards (precision 1 mm).

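### The primary outcome is LAZ at 24 months, but the analysis section tests it at nine ages in four arms, with no age named as confirmatory and only a 5% alpha stated

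*Protocol article*

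**What the plan says.** **Endpoint.** The Primary outcomes section fixes one age: "The primary outcome measure will be the LAZ of children at 24 months of age". The abstract's Methods paragraph powers that outcome at 24 months, for the difference "between the comparison arm and each intervention arm".

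**Analysis.** The Statistical analysis plan section attaches the primary-outcome label to a longer list: "Data analysis to detect change of the primary outcome (mean LAZ) will be conducted with length measured at 1, 3, 6, 9, 12". The full list is "length measured at 1, 3, 6, 9, 12, 15, 18, 21 and 24 months of age using t-tests". No age is given precedence, and the eight ages before 24 months are not called secondary or descriptive. The section also plans a log-rank test, a Cox model for each arm, and multiple linear regression for mean LAZ change in each arm. Random effects for clustering are promised for the regression models and not mentioned for the t-tests.

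**Arms.** The aim is stated for bundles in general: "We hypothesised that our intervention bundle(s) would cause a change of at least 0.4 in mean LAZ of children". The abstract's Discussion expects evidence on "which bundle(s) can have significant effect on linear growth of children". No arm is named as the main contrast.

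**Error rate.** The only level given is in the sample size section: "As the third assumption, we considered an 80% power and 5% alpha". Sidedness is not stated, and no division of alpha over arms or ages appears.

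**The concern.** The definition of the primary outcome and its analysis do not match. One section gives a single age. The other gives nine, all described as analyses of the primary outcome. Followed literally, that is 4 arms × 9 ages = 36 t-tests, with the regression of mean LAZ change in addition.

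The 5% level entered the sample size as the level of one comparison. It is not the error rate of a conclusion about which of four bundles works, and still less of one that could draw on any of nine ages. The results are meant to inform the choice of interventions, so a reader of the final report needs to know beforehand which result decides.

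Two features make the t-test list a poor primary analysis. The complementary food supplement (CFS) starts at 6 completed months. At 1 and 3 months, therefore, arm 1 has received the same components as arm 2, and arm 3 the same as arm 4, so those tests cannot bear on the CFS component. The t-tests are also the one listed method for mean LAZ to which the cluster random effects are not extended.

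**Working it through.** **Inputs from the article (Sample size).** Difference 0.4; SD 1; intra-cluster correlation 0.06; alpha 5%; power 80%; 25 clusters per arm; 175 children in each intervention arm and 350 in the comparison arm at 24 months. That is 175/25 = 7 and 350/25 = 14 children per cluster.

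**Assumptions not in the article.** Tests are two-sided. No bundle has any effect. LAZ correlates 0.98, 0.95 or 0.90 from one month to the next, decaying with the gap in age. Between 1 and 24 months these give correlations of 0.98²³ = 0.63, 0.95²³ = 0.31 and 0.90²³ = 0.09, so the last is near the pessimistic end.

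**The plan's own sample size.** Per arm before clustering: 2 × ((1.960 + 0.842)/0.4)² = 98.1. With 7 per cluster the design effect is 1 + 6 × 0.06 = 1.36, giving 98.1 × 1.36 = 133.4, so 134 and not the stated 175. The figure of 175 appears with 14 per cluster (98.1 × 1.78 = 174.6), which the text does not state. The difference is on the large side and does not affect this point. The losses do reproduce: 11% + 4% + 15% = 30%, and 250 × 0.70 = 175.

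**Standard error and correlation of the contrasts at 24 months.**
- Intervention arm: 1.36/175 = 0.00777.
- Comparison arm: design effect 1 + 13 × 0.06 = 1.78; 1.78/350 = 0.00509.
- Variance of one contrast: 0.00777 + 0.00509 = 0.01286; SE = 0.1134.
- Correlation between two contrasts sharing the comparison arm: 0.00509/0.01286 = 0.396.

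**Chance of at least one false positive, each test at 5%** (multivariate normal simulation, correct cluster SEs):

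| Tests that count | Either direction | In favour of a bundle |
|---|---|---|
| 4 contrasts at 24 months | 16.6% | 8.3% |
| All 36, monthly correlation 0.98 | 41% | 21% |
| All 36, monthly correlation 0.95 | 54% | 28% |
| All 36, monthly correlation 0.90 | 65% | 36% |

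For scale, four independent tests would give 1 − 0.95⁴ = 18.5%. Thirty-six would give 1 − 0.95³⁶ = 84%, an upper bound that does not apply here, because ages repeat within a child and arms share a comparator.

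**If the t-tests ignore clustering.** The four 24-month tests alone give about 33% in either direction.

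**Power per arm for 0.4.** The standardised effect is 0.4/0.1134 = 3.53.
- Unadjusted: Φ(3.53 − 1.96) = 94%.
- Dunnett, critical value 2.46: Φ(3.53 − 2.46) = 86%.
- Bonferroni, 0.05/4 = 0.0125, critical value 2.50: Φ(3.53 − 2.50) = 85%.

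**The case against.** The endpoint is stated consistently. The title, the abstract, the aim and the Primary outcomes section all point to 24 months or two years, and the list of ages may be meant to describe the growth curve. This is a fair reading, and probably the intended one. The analysis section does not say so, however: it introduces the whole list as the analysis of the primary outcome.

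A reader might infer that a bundle would be recommended on one significant age or one significant arm. The documents do not support that. The sentence about which bundles work is an expectation in the abstract, not a decision rule, and no section says that significance at a single age would suffice.

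A reader might also infer that the tests will certainly be unadjusted. That would rest on silence. The full analysis plan is not shown and could contain a multiplicity procedure.

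Nor do the figures show that a false claim for some bundle is more likely than not. Only two-sided errors pass one half, and only in part of the assumed correlation range. They include bundles falsely found worse than comparison, which nobody would recommend. In the favourable direction the figure stays between about 21% and 36%, on a correlation range that has no source in the article.

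Finally, whether four contrasts, each powered separately, need family-wise control is a matter of debate. This stands as a caution on that part of the fix. It does not touch the mismatch between endpoint and analysis.

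**Conclusion.** The point holds as a mismatch in the printed text. One age defines the primary outcome, nine ages are tested as the primary outcome, none is confirmatory, and the only level given is 5%. An analysis plan not shown here may settle it, but the article as written does not.

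With no true effect, two-sided 5% tests and correct cluster SEs, the error for the family is about 17% at 24 months alone and roughly 40% to 65% if any age may count. The favourable-direction figures are about 8% and about 21% to 36%. The 24-month figures depend only on the plan's inputs and two-sidedness. The all-ages figures also depend on the assumed monthly correlation of 0.98 to 0.90.

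This should be fixed. It is not a fatal flaw: the primary age is clear elsewhere in the article, and the repair is a matter of wording.

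**What to change.** In the Statistical analysis plan section:

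1. Name LAZ at 24 months as the only confirmatory analysis, taken from the cluster-adjusted model rather than a t-test, for the four arm-versus-comparison contrasts.
2. Control those four contrasts at a family-wise 5% by Dunnett or Holm.
3. Replace the separate t-tests at the other eight ages by one longitudinal mixed model (visits within child within cluster). Report arm-by-age estimates with confidence intervals as supportive. This model also uses the earlier measurements of children lost before 24 months.

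**Cost.** Wording in the analysis plan, and some power: from about 94% to about 86% per arm with Dunnett (85% with Bonferroni) under the plan's own inputs. That is still above the stated 80%, with no more children needed. Item 2 is the more debatable; items 1 and 3 stand without it.

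### The t-test named for the primary outcome and the log-rank test for stunting make no allowance for the randomised clusters, and the plan does not say whether they or the regression models decide

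*Protocol article*

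**What the plan says.** The Cluster randomization and intervention allocation section describes 125 clusters allocated in 25 blocks of five, so 25 clusters per arm, with equal numbers per arm within each union. The Sample size section allows for clustering: it takes "the inter-cluster correlation coefficient of 0.06", which it says was "derived from the design effect for HAZ in BDHS 2011, was used for adjustment of clustering effects".

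The Statistical analysis plan section then sets out these analyses:

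- Detection of a change in the primary outcome, mean LAZ, at nine ages from 1 to 24 months, "using t-tests assuming LAZ will satisfy the normality assumption".
- Assessment of significance for stunting over time, which "will be done by the log rank test", followed by a Cox model for each intervention arm.
- Multiple linear regression to quantify each arm's effect on LAZ and on some continuous secondary outcomes, and logistic regression for binary outcomes.
- One sentence on clustering: "For regression models, we shall consider random effects of clustering".

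**The concern.** The clustering sentence is limited to regression models. It can reach the linear regression of LAZ and, by extension, the Cox model. It does not reach the t-test or the log-rank test, which are the analyses given the task of detecting an effect.

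A child-level t-test treats 175 and 350 children as independent, although they come in groups of about 7 and 14. Unless all of the between-cluster variance is removed by the blocking, its standard error is too small and its p-values are too low. The same LAZ outcome also gets a second p-value from the regression, and nothing says which one counts if the two disagree. The trial is meant to guide the choice among bundles, so a bundle with no effect could be called effective more often than the stated 5%.

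**Working it through.** **Inputs (Sample size section unless noted).** Difference 0.4 ("a 0.4 difference in mean LAZ score was expected in intervention arms compared to comparison"); SD 1 ("standard deviation of mean LAZ in both intervention and comparison arms will be 1"); ICC 0.06; 80% power and 5% alpha, taken as two-sided because the sidedness is not stated; 175 children per intervention arm and 350 in the comparison arm. Twenty-five clusters per arm (allocation section) give 175/25 = 7 and 350/25 = 14 children per cluster.

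**The plan's own figure.** Without clustering, n = 2 × ((1.96 + 0.84)/0.4)² = 98.1 per arm (unrounded normal quantiles). With design effect 1 + (m − 1) × 0.06 and m = 14, this is 98.1 × 1.78 = 174.6, which rounds up to the stated 175. The article does not state which m was used. With m = 7, the need is 98.1 × 1.36 = 133.4. The planned size therefore does include clustering, with room to spare.

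**Variance of a difference between one intervention arm and comparison.**
- Design effects: 1 + 6 × 0.06 = 1.36 and 1 + 13 × 0.06 = 1.78.
- True variance: 1.36/175 + 1.78/350 = 0.01286, SE 0.113.
- Variance used by a child-level t-test: 1/175 + 1/350 = 0.00857, SE 0.093.
- Ratio 1.50. The SE is understated by 1 − 1/√1.50 = 18%.
- Actual size: 2 × (1 − Φ(1.96/√1.50)) = 10.95%. A simulation of 40,000 trials gave 11.1%. A t-test on the 25 versus 25 cluster means, in the same simulation, gave 5.1%.

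**Effect of blocking.** The calculation above puts no between-cluster variance between blocks. Each block holds one cluster per arm, so a block component cancels from the difference. If a fraction f of the 0.06 lies between blocks, the true variance is 2 × 0.06 × (1 − f)/25 + 0.94/175 + 0.94/350.

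| f | True variance | Ratio to 0.00857 | Actual size |
|---|---|---|---|
| 0 | 0.01286 | 1.50 | 11.0% |
| 0.25 | 0.01166 | 1.36 | 9.3% |
| 0.50 | 0.01046 | 1.22 | 7.6% |
| 0.75 | 0.00926 | 1.08 | 5.9% |
| 1 | 0.00806 | 0.94 | 4.3% |

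The documents do not give f.

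**Other ICC values, with f = 0.** Size 7.0% at ICC 0.02, 9.0% at 0.04 and 14.8% at 0.10.

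**Log-rank test.** Its size depends on how LAZ evolves and how the ICC carries over to time to stunting. The documents give neither. As an illustration only, a simulation that assumed mean LAZ falling from −1.0 at 1 month to −2.0 at 24 months, 70% of the variance persistent within a child, and f = 0 gave 4.9%, 8.8% and 11.1% for cluster ICC 0, 0.03 and 0.06.

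**Power after correction.** 0.4/√0.01286 = 3.53, so power is Φ(3.53 − 1.96) = 94%, or 93% with a t reference on 48 degrees of freedom.

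**The case against.** The case for the plan has four parts.

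- *A cluster-adjusted LAZ analysis is already there.* The linear regression estimates each arm's effect on LAZ, and the random-effects sentence applies to it. The Cox model after the log-rank test can likewise carry a frailty term. This stands. A reader might infer that the plan ignores clustering altogether, and the text does not support that. What remains is an unadjusted test beside a model that can be adjusted, with no statement of which decides.
- *The verb in the random-effects sentence is not a hedge.* Elsewhere the authors use it for steps that were carried out, as in "we considered an 80% power and 5% alpha". This is a fair reading, and the firmer wording asked for below is a clarification. It does not extend the sentence to the t-test or the log-rank test.
- *The unit of the t-test is not stated, and a t-test on cluster means would be valid.* This is true. The child-level reading is the more natural one, because normality is assumed for LAZ itself and clustering is mentioned only for regression, but it remains an inference. If cluster means were intended, the text needs to say so.
- *The blocking, and the homogeneity expected in the Discussion, reduce the inflation.* This stands as to size. The survey-based ICC of 0.06 may include variation that the blocks remove. The 11% is the upper end at that ICC, not a point estimate.

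Two further inferences go beyond the documents. One is that the log-rank test also runs at 11%, which rests wholly on an assumed growth path. The other is to multiply up over the four comparisons with the comparison arm, which gives about a 33% chance of at least one false claim. About 17% would arise from four unadjusted comparisons with correct standard errors, so that figure does not measure this defect and the fix would not remove it.

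**Conclusion.** The point holds. As written, the tests that are to detect the effects on LAZ and stunting do not match the randomised unit or the sample size calculation, and the plan does not rank them against the models that can. For the t-test the consequence is a standard error too small by up to 18% and a two-sided type I error of up to about 11%, per comparison and per age. This assumes child-level testing, ICC 0.06, SD 1 and the planned 7 and 14 children per cluster. The excess shrinks as more of the between-cluster variance lies between blocks, and disappears if all of it does. For the log-rank test only the direction can be stated, with the same proviso about blocking. Because this is the test named for the primary outcome, it should be corrected before the analysis.

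**What to change.** 1. Name one primary test of LAZ at 24 months. Either use the linear mixed model already foreseen, with a random intercept for cluster, block terms and small-sample degrees of freedom, or use a t-test on cluster means. Drop the child-level t-tests.
2. Reword the random-effects sentence as a commitment to include them in every regression model, and say that it covers the Cox model.
3. Base the stunting inference on the planned Cox model with shared frailty or cluster-robust variance, or replace the log-rank test by a clustered version.

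The cost is a few sentences. According to Trial status, recruitment is complete and data collection is ongoing, so trial conduct is unaffected. Intervals will generally be wider than those of a child-level t-test, and correct. Power for 0.4 LAZ remains about 93%, above the planned 80%.
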